#### Intervention fidelity

Intervention fidelity will be measured in terms of 1) percentage of occasions participants on the systematic voiding programme either self-initiated toileting or were prompted to toilet by ward staff within 30 minutes of the prescribed voiding interval and 2) accuracy of programme implementation, assessed by percentage of episodes where there was complete adherence to the elements of the protocol for the relevant conservative intervention (bladder training, prompted voiding and pelvic floor muscle training).

Data will be extracted from recording sheets specific to each route on the programme.

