## Background

Urinary incontinence following acute stroke is common, affecting between 40%-60% of people in hospital after a stroke; 25% at hospital discharge and 15% after one year [1]. In longer term stroke survivors, the prevalence has been reported as 17% [2]. Urge incontinence is the most common type after stroke [3], but the cerebral lesion may also lead to practical difficulties with bladder control caused by, for example, motor impairment, depression and aphasia [4] (termed functional incontinence). Despite the availability of clinical guidelines for the management of urinary incontinence in general [5] and urinary incontinence after stroke [6], national audit data [7] suggest incontinence is often poorly managed.

Our systematic review [8] found no rigorously conducted studies evaluating interventions designed to manage urinary incontinence after stroke in secondary care. The intervention in our programme will focus on conservative strategies shown to have some effect with participants in studies included in Cochrane systematic reviews [9-13], but which have not had their effectiveness demonstrated with stroke patients. These strategies are a combined package of bladder training and (where possible) pelvic floor muscle training, and prompted voiding.

Available conservative interventions for urinary incontinence include bladder training, timed voiding, prompted voiding, habit retraining and pelvic floor muscle training. Bladder training is generally used for urge incontinence and aims to increase the time interval between voids so continence is regained. It involves patient education, scheduled voiding, and positive reinforcement, but can also include self-monitoring and urge suppression techniques. Prompted voiding and timed voiding have mainly been used with people who have cognitive deficits. They are based on a system of scheduled voids, with prompted voiding including reminders and reinforcement for self-initiation of toileting. To date, trials of prompted voiding have mainly taken place in United States nursing homes; however there is no a priori reason why this approach should not be introduced into the care of stroke patients in secondary care in the UK.

Pelvic floor muscle training may also be effective in assisting the individual to manage urge, stress or mixed incontinence [10], and has been shown to be effective as a combined intervention with bladder training [14,15].

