The effectiveness of conservative interventions has been systematically reviewed in adults. In the review of bladder training [11], trials tended to favour bladder training and there was no evidence of adverse effects. The review of prompted voiding [9] found evidence of increased self-initiated voiding and decreased incontinent episodes in the short-term.

Despite a growing evidence-base, existing evidence has not been widely implemented in clinical practice, even by stroke specialist teams working on recognised stroke units [16]. This lack of implementation in stroke clinical practice is in keeping with a recent and growing recognition that the implementation of research in practice is influenced not only by individual clinicians but also by the organisational context in which they operate [17-22]. Organisational context has been defined as "the environment or setting in which the proposed change is to be implemented" [23]. At its simplest level, context may refer to the physical environment where health care takes place. However, Rycroft-Malone et al. concluded from their concept analysis that contexts conducive to research implementation included a range of less tangible process elements: "clearly defined boundaries; clarity about decision-making processes; clarity about patterns of power and authority; resources; information and feedback systems; active management of competing "force fields" ... and systems in place that enable dynamic processes of change and continuous development.' [23].

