### Objectives

The trial objectives are to:

• assess feasibility in terms of rates of participant recruitment and retention

• assess fidelity to the intervention

• conduct a qualitative assessment of feasibility from the perspective of multiple stakeholders

• conduct a preliminary evaluation of supported implementation compared with implementation alone

• investigate patient-related factors affecting patient outcome

• investigate stroke service-level factors potentially affecting stroke service outcomes to estimate the amount of unexplained variability in outcomes between Trusts and between patients

• confirm the choice of primary and secondary outcome measures for a full-scale cluster-randomised trial to evaluate effectiveness

• develop and test data collection tools for an economic evaluation within a full-scale cluster-randomised trial

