### Interventions

#### Systematic voiding programme

The intervention will comprise algorithm-driven individualised systematic voiding programmes tailored to the physical and cognitive capabilities of each patient The algorithm specifies two routes: a combined package including bladder training and pelvic floor muscle training for those patients who are cognitively able, and prompted voiding for those with cognitive impairment. Bladder training will include three main components: 1) focused education for patients and carers (including information on the anatomy and physiology of the lower urinary tract, the rationale behind the programme and strategies to suppress the urge to void, for example distraction and relaxation [15,40]); 2) individualised voiding regimens designed to restore normal voiding patterns by progressively lengthening the time interval between voids, based on assessment of participants' normal voiding patterns and self-monitoring; 3) patient-held voiding diary, a cognitive intervention designed to promote self-awareness of voiding habits [41,42].

Pelvic floor muscle training is designed to strengthen types I and II muscle fibres in the pelvic floor. Patients will be instructed to perform 5 fast (3 seconds) and 10-20 sustained (10 seconds) contractions with 10 second relaxation periods between contractions twice a day.

For those patients with cognitive impairments, the programme will consist of elements traditionally classified as prompted voiding: participants will be approached according to individualised schedules (for example every two hours during waking hours), asked if they are wet or dry, and prompted to use the toilet [43]. Verbal praise will be offered for correct reporting of dryness/wetness and successful toileting. Participants with cognitive impairments will be given the opportunity to participate in the education and patient-held diary components of the intervention.

Participants not able to walk to the toilet will be assisted by nursing staff. Participants will be provided with written information about their systematic voiding programme to enable them to continue with it after discharge from hospital.

The intervention has been informed by the findings of an evidence synthesis on the barriers and enablers to successful implementation of conservative interventions for UI completed during the programme's Development Phase, in line with the MRC Framework for developing and evaluating complex interventions [44,45].

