#### Intervention fidelity data

For the intervention groups, fidelity measures will be summarised using mean (with standard deviation) or median (inter-quartile range), depending on the distributions of the percentage fidelity measures. Fidelity will be compared across intervention groups and across different conservative interventions (i.e. bladder training, prompted voiding and pelvic floor muscle training).

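### The first fidelity measure pools patients' self-initiated toileting with timely staff prompting, so a difference between arms or routes cannot be attributed to staff delivery

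*Protocol article*

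**What the plan says.** In the protocol article, Outcomes, Intervention fidelity, the first measure is the percentage of occasions on which participants on the programme "either self-initiated toileting or were prompted to toilet by ward staff within 30 minutes of the prescribed voiding interval". The second is the "percentage of episodes where there was complete adherence to the elements of the protocol for the relevant conservative intervention".

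Under Data analysis, Intervention fidelity data, "fidelity measures will be summarised using mean (with standard deviation) or median (inter-quartile range"), and "Fidelity will be compared across intervention groups and across different conservative interventions". That section states neither a separation of the two ways an occasion can count nor an adjustment for case mix. Patient-level covariates are stated only for the outcome models (Data analysis, Outcomes).

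Three other places bear on the point:

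- Background describes self-initiation in two ways. The review of prompted voiding "found evidence of increased self-initiated voiding and decreased incontinent episodes in the short-term", which makes it a patient response. The same section describes "prompted voiding including reminders and reinforcement for self-initiation of toileting", which makes it something staff encourage.
- Systematic voiding programme assigns the route by cognitive ability: bladder training with pelvic floor muscle training for patients who are cognitively able, prompted voiding for those with cognitive impairment.
- Objectives include assessing fidelity, and also to "conduct a preliminary evaluation of supported implementation compared with implementation alone".

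**The concern.** An occasion counts as faithful either because the patient went without a prompt or because staff prompted in time. Only the second is directly something the ward did. The first depends partly on how able the patient is and how far he or she has recovered.

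The arm comparison is exposed to this. There are four services per arm, and the staff who recruit know the allocation (Allocation concealment). The section on patient recruitment itself anticipates that clusters may differ in the severity of the patients they enrol. The route comparison is exposed by design, because patients are sorted into routes by cognitive ability, which plausibly affects whether they self-initiate.

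At stake is the reading of supported implementation against implementation alone. Fidelity speaks closely to whether support changes ward practice. A pooled percentage could differ between arms with identical prompting by staff, or could hide a real difference in prompting.

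**Working it through.** The article reports no fidelity figure, and its sample size is stated to be pragmatic, so there is no figure of the plan to reproduce. The check asks how far the pooled percentage moves when staff prompting is held equal.

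**Inputs, all assumed:**

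- s, the share of prescribed occasions that the patient self-initiates: 20% in one group, 40% in the other.
- p, the share of remaining occasions that staff prompt on time: the same in both groups, from 30% to 90%.
- w, the share of self-initiated occasions that fall inside the tolerance: 50%. It is needed only if the 30 minutes governs self-initiation as well as prompting, which the sentence leaves open.

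**Three readings of the measure F:**

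- A. Any self-initiated occasion counts: F = s + (1 − s)p.
- B. Self-initiation counts only inside the tolerance, and staff prompt all other occasions at rate p: F = sw + (1 − sw)p.
- C. As B, but staff do not prompt a patient who has already gone outside the tolerance: F = sw + (1 − s)p.

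Worked example for A at p = 50%: 0.20 + 0.80 × 0.50 = 0.60, and 0.40 + 0.60 × 0.50 = 0.70, a gap of 10 points.

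| p in both groups | A: s = 20% vs 40% | B: s = 20% vs 40% | C: s = 20% vs 40% |
|---|---|---|---|
| 30% | 44% vs 58% (+14) | 37% vs 44% (+7) | 34% vs 38% (+4) |
| 50% | 60% vs 70% (+10) | 55% vs 60% (+5) | 50% vs 50% (0) |
| 70% | 76% vs 82% (+6) | 73% vs 76% (+3) | 66% vs 62% (−4) |
| 90% | 92% vs 94% (+2) | 91% vs 92% (+1) | 82% vs 74% (−8) |

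The gap is 0.20 × (1 − p) under A, 0.20 × w × (1 − p) under B, and 0.20 × (w − p) under C. Under A and B it is positive throughout this range and largest where prompting is poorest. Under C it changes sign once p exceeds w.

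**Components shown separately.** On-time prompts among occasions not self-initiated equal p in both groups, for example 50% vs 50%, a gap of 0. The percentage self-initiated shows 20% vs 40%. The source of the pooled gap is then visible. This result requires p not to depend on how able the patient is.

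**The case against.** The strongest reply is that self-initiation belongs to the programme. Bladder training is largely patient-led, with education, self-monitoring, a patient-held diary and regimens built on "progressively lengthening the time interval between voids". Prompted voiding includes reinforcing self-initiation. A patient who goes on schedule without a prompt is following the programme, and staff may have brought that about. This stands: the pooled figure is a fair measure of adherence to the voiding schedule, and part of any difference may be staff-made. But the pooled figure cannot show which part.

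The second fidelity measure is a partial safeguard, since it does not name self-initiation as a success. It does not make the first measure interpretable, and the planned comparison covers both.

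The components may also be tabulated in an analysis plan that is not shown, and the recording sheets may already separate them. The point therefore rests only on what the article fixes, namely the pooled definition and a comparison of fidelity across arms and routes.

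Replacing the pooled measure with prompts among occasions not self-initiated would go too far. Those occasions form a subset selected after randomisation, which shrinks as patients improve and leaves the more dependent ones. A ward would also get no credit for teaching patients to go unprompted.

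A reader might infer more in two places. One inference is that a fixed 30-minute tolerance biases the route comparison because bladder training intervals are longer. The article's only interval is a two-hour example for prompted voiding. It does not say that bladder training intervals are longer, and regimens start from each patient's assessed pattern. The other inference is that relating fidelity to continence would be circular. The analysis sections plan no such analysis.

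**Conclusion.** The concern holds in a limited form. A difference between arms or routes in the first fidelity measure cannot be attributed to staff delivery, because the measure also moves with how often patients self-initiate. With equal staff prompting and assumed self-initiation of 20% against 40%, the gap is 2 to 14 points if any self-initiation counts. If the tolerance also governs self-initiation and half of such occasions meet it, the gap is 1 to 7 points, or runs from +4 to −8 if patients who went off schedule are not then prompted.

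It is tempting to conclude that fidelity must rise as patients recover, or that a difference between the arms would be an artefact. The article supports neither. The direction depends on an unstated reading of the tolerance, and staff can themselves raise self-initiation. The values of s, p and w are illustrations, not estimates. The primary effectiveness outcome is unaffected. What is weakened is the evidence on supported implementation against implementation alone.

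**What to change.** Keep the pooled percentage and describe it as adherence to the voiding schedule. State whether the 30-minute tolerance applies to self-initiated toileting or only to prompts. In both the arm and the route comparison, also report:

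- (a) on-time staff prompts as a percentage of prescribed occasions not self-initiated;
- (b) the percentage of prescribed occasions self-initiated.

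Treat (a), read together with (b) and the second fidelity measure, as the evidence on staff delivery.

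The cost is a little more tabulation and, if the recording sheets do not already distinguish the two kinds of occasion, one tick box. Component (a) rests on fewer occasions in a selected, more dependent group, which is why it should accompany the pooled figure and not replace it.

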#### Ascertainment of outcomes

Presence/absence of incontinence will be measured by the International Consultation on Incontinence Questionnaire (ICIQ-UI Short Form) [51]. Absence of incontinence will be defined as the response 'never' to Question 3, 'How often do you leak urine?'; presence of incontinence will be defined as any other response to Question 3 (ranging from 'about once a week or less often' to 'all the time'). The ICIQ-UI Short Form has received a grading of A^new ^- highly recommended from the International Consultation on Incontinence Symptoms and Quality of Life Committee indicating published reports of acceptable reliability, validity and responsiveness in at least one study [52]. To our knowledge, the ICIQ-UI Short Form has not been used in the post-stroke population. We have conducted preliminary validation of the tool with six stroke survivors from our Patient, Public and Carer Involvement Group using the approach recommended by the ICIQ developers ([name], personal communication); all thought the tool was appropriate for use post-stroke and few problems were identified.

Quality of life will be measured using the Incontinence Quality of Life Instrument (I-QOL) [53,54] and the EuroQol (EQ-5D) [55]. Frequency and severity of incontinence will be ascertained using the Incontinence Severity Index [56]. Urinary symptoms will be measured using the Leicester Urinary Symptom questionnaire [57] and activities of daily living via the Barthel Index [58].

In addition, the following baseline information about the patient will be recorded following consent: date of birth (age to be calculated*); sex; ethnicity; date of admission; date of stroke onset; date baseline questionnaire completed; location when recruited into the study; consciousness level (defined as either 'alert' or 'drowsy' on the 'Clinical Status on Admission' item of the European Stroke Database); side of body affected by stroke; type of stroke; location of stroke (OCSP classification[59]); co-morbidities (Charlson Comorbidity Index[60]; day seven Barthel Index [58]; pre-stroke Modified Rankin Scale [61]*; pre-stroke living circumstances*; Leicester Urinary Symptom questionnaire [57]; type of UI (urge UI, mixed UI, 'functional' UI or unclear); cognitive ability (6 Item Cognitive Impairment Test [62]); fluid intake; bowel function; relevant clinical investigations (e.g. mid stream urine, bladder scan); medications; living circumstances; verbal sub-section of the Glasgow Coma Scale [63]*; ability to lift both arms off the bed*; ability to walk independently*; ICIQ-UI Short Form [51]; Incontinence Severity Index [56]; EuroQol (EQ-5D) [55].

The six factors highlighted with a * above from the Edinburgh stroke case mix adjuster [64] will be collected to enhance patient-level adjustment for prognosis.

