#### Inclusion criteria for patients

Patients aged 18 or over who have a diagnosis of stroke based on the WHO criteria [36] will be included in the study, with no upper age limit. Patients are required to have urinary incontinence (UI) as defined by the International Continence Society [37] as "involuntary loss of urine" and to have incontinence classified as stress UI, urge UI, mixed UI or 'functional' UI **OR **to be catheterised in the acute phase of the stroke; to be conscious (defined as either 'alert' or 'drowsy' on the 'Clinical Status on Admission' item of the European Stroke Database), and to be medically stable as judged by the clinical team.

Participants who had incontinence before the index stroke will be included. Given the expected age range of the population, there is likely to be a high prevalence of pre-stroke incontinence among potential participants. Furthermore, there is evidence to suggest patients with longstanding incontinence may benefit from a programme of behavioural interventions [9,11].

Participants who are catheterised will be recruited; if the catheter is removed, they will be assessed as per protocol and begin the systematic voiding programme if they are still incontinent. Participants who are continent after catheter removal and those discharged with a catheter still in situ will not be put onto the programme. Data from these participants will be analysed separately from participants who have taken part in the programme.

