#### Data collection

Baseline data will be collected on entry to the trial by the research nurse. Outcome data will be collected at six weeks, three months and (for participants recruited within the first three months of the trial) twelve months post-stroke via postal questionnaires (or hand-delivered questionnaires if participants are still in hospital at six weeks). All participants with aphasia will be offered a face-to-face interview with the research nurse to collect outcome data; this will be conducted using appropriate communication aids (e.g. pictorial cards with a 'thumbs up' picture indicating 'yes' and a 'thumbs down' card indicating 'no'). Specialist help will be available from Speech and Language Therapists and Speakeasy, a specialist aphasia charity based in Ramsbottom, Bury (http://www.buryspeakeasy.org.uk/), if this is needed.

Postal and telephone reminders will be used if questionnaires are not returned within two weeks. Where completion of postal questionnaires is not possible, participants (or carers if a proxy is needed) will be invited to complete assessments over the telephone. If neither postal or telephone completion is possible, a face-to-face assessment in the participant's home will be offered.

We will collect intervention fidelity data for all participants in the active intervention groups during three (for sites with a nine month intervention period) or four (for sites with a 12 month intervention period) randomly selected weeks during each three-month period in which the stroke service is recruiting participants into the trial.

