#### Outcomes

The primary analysis set will be defined as the intention-to-treat population. All stroke services randomised will be retained in the trial. Outcome data will be collected from all consented patients whenever possible, whatever their level of subsequent engagement with the allocated intervention programme. If there is more than 10% loss to follow-up overall or moderately differential loss to follow-up across stroke services, a secondary per-protocol analysis will also be considered. The decision as to whether a per-protocol analysis will be informative will be made by the trial statistician in conjunction with other members of the Trial Management Group; this decision will be made without reference to the recorded values of the outcome data.

To account for the cluster randomisation, we shall use mixed effects modelling for continuous, ordinal and dichotomous outcomes to compare the two groups on primary and secondary outcome data. Baseline measures of the outcomes variables (where appropriate), stroke classification, type of incontinence and the other prognostic patient-level information (from the Edinburgh case-mix adjuster) will be included as individual-level covariates in the models for outcome data.

Missing outcome data will be imputed according to the particular outcome. For the primary analysis, dichotomous and ordinal outcomes for those who withdraw, die or are otherwise lost to follow-up will be imputed using a worst-case scenario (e.g. for the primary outcome variable, all those for whom incontinence status is not recorded at 6-weeks post-stroke will be assumed to be incontinent). For continuous outcomes, the primary analysis will use a non-parametric multiple imputation approach [66].

The effect of stroke service-level factors will also be explored in the modelling; this will enable appropriate stratification to be used in the future larger scale trial, if desired, and to potentially reduce the size of the intra-stroke service correlation coefficient by reducing the unexplained component of the variability between stroke services. This analysis will be used to confirm the sample size necessary for the future trial and to provide estimates (including 95% confidence intervals) of the effectiveness of each intervention relative to usual care.

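### The primary outcome rule counts a catheterised participant who does not leak as continent, and the plan's separate analysis of catheterised patients only partly deals with this

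*Protocol article*

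**What the plan says.** Under *Ascertainment of outcomes* the primary outcome has two categories, both read from Question 3 of the ICIQ-UI Short Form: "Absence of incontinence will be defined as the response 'never' to Question 3, 'How often do you leak urine", while "presence of incontinence will be defined as any other response to Question 3". There is no condition on catheter use and no third category.

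Under *Inclusion criteria for patients*, catheterisation is a route into the trial in its own right, as an alternative to a classified type of incontinence: "to be catheterised in the acute phase of the stroke". The section confirms that "Participants who are catheterised will be recruited". It foresees that some will keep the catheter: "those discharged with a catheter still in situ will not be put onto the programme". Of these, and of those who are continent once the catheter is out, it says: "Data from these participants will be analysed separately from participants who have taken part in the programme".

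Under *Data analysis, Outcomes*: "The primary analysis set will be defined as the intention-to-treat population". Outcomes are sought from every consented patient regardless of engagement with the programme. Participants whose 6-week status is unrecorded are taken to be incontinent.

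*Data collection* provides for people who are inpatients at the primary time point: "or hand-delivered questionnaires if participants are still in hospital at six weeks".

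**The concern.** Someone whose bladder drains through a catheter can truthfully answer *never*. The written rule then records absence of incontinence, although bladder control has not been shown. These participants are a planned part of the population.

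Two things are at stake. First, if catheter use at six weeks differs between arms, part of the estimated effect reflects catheter use and not regained continence. Secondly, even if catheter use is the same in all arms, the incontinence rate is lower than it would be if catheter users were not counted as continent. That rate feeds the design of the full trial, and informing that design and confirming the outcome measures are stated purposes of this pilot.

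**Working it through.** **Does another provision catch the case?**

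1. *Worst-case imputation.* It applies only where status is not recorded. A recorded *never* passes through. A blank from a catheterised participant is scored incontinent, so two people in the same clinical state can be scored in opposite ways.
2. *Separate analysis.* It sets no outcome coding. It covers people discharged with a catheter and people continent after removal. It does not cover people still in hospital with a catheter at six weeks, or people catheterised again later.
3. *Its comparator.* The contrast is with those who took part in the programme. Usual care has no programme. The article does not say whether the same patients are to be set apart in that arm.
4. *The analysis set.* Intention to treat with outcomes from all consented patients includes those discharged with a catheter. The article does not say which statement governs the primary analysis.

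**Arithmetic.** The article gives no catheter prevalence and no continence rates, so there is no plan figure to reproduce on this point. All rates below are assumptions. For one arm, let *c* be the share with a catheter at six weeks, *s* the share of those answering *never*, and *p* the share continent among the uncatheterised.

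- Current rule: proportion scored continent = c·s + (1 − c)·p
- Catheter counted as not continent: (1 − c)·p
- If *s* is the same in both arms, the two codings differ in the between-arm difference by (difference in c) × s.

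Worked case: c = 10% in arm A and 2% in arm B, p = 40% in both, s = 1.

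- Current rule: A = 0.10 + 0.90 × 0.40 = 46.0%; B = 0.02 + 0.98 × 0.40 = 41.2%. A appears better by 4.8 points.
- Catheter as not continent: A = 0.90 × 0.40 = 36.0%; B = 0.98 × 0.40 = 39.2%. B appears better by 3.2 points.
- Gap between codings: 4.8 + 3.2 = 8.0 points = (10% − 2%) × 1.

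Other assumed cases with s = 1, shown as B minus A in points:

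| c, A v B | p, A v B | Catheter = continent | Catheter = not continent |
|---|---|---|---|
| 10% v 10% | 30% v 40% | +9.0 | +9.0 |
| 10% v 5% | 30% v 40% | +6.0 | +11.0 |
| 15% v 5% | 30% v 40% | +2.5 | +12.5 |
| 15% v 5% | 40% v 40% | −6.0 | +4.0 |

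When p is equal in both arms, the false difference under the current rule is (difference in c) × (s − p). At s = 1 this is 0.08 × 0.60 = 4.8 points. At s = 0.5 it falls to 0.08 × 0.10 = 0.8 points. The worked case is therefore an upper limit for those prevalences and that p.

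With equal prevalence the difference is unaffected, but the level is. At c = 10% and p = 30%, the incontinence rate is 100 − (10 + 27) = 63% under the current rule and 73% if catheter users count as not continent. The understatement is c·s, at most 10 points here.

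In head counts, an average arm has 780/3 = 260 participants. An assumed 5%, 10% or 15% with catheters is 13, 26 or 39 people.

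**The case against.** The case on the other side has four parts.

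- *The rule matches the trial's own definition.* Incontinence is defined as involuntary loss of urine, and being catheterised is listed as an alternative to it. A person who does not leak is not incontinent in that sense. This stands as far as it goes: adding a catheter condition is a choice of estimand. But the article should make that choice openly, and it never says that a catheter user counts as a success.
- *The largest foreseeable group is already set apart.* This is partly right. Those discharged with a catheter are named, but the provision leaves the gaps listed above.
- *A condensed article need not list every questionnaire item or coding rule.* This also stands. One cannot infer that catheter status goes unrecorded at follow-up, and the analysis plan may say more. But the outcome rule is not left open: it is stated in full, and as stated it gives this result.
- *Counting a catheter as failure also moves the result.* This is correct. In the worked case it creates a 3.2-point difference with no difference among the uncatheterised, so no single coding is neutral when catheter use differs by arm.

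A reader might also infer that the rule favours usual care, on the view that a continence programme leads wards to remove catheters sooner. The documents do not support this. The programme described has no catheter-removal component, and assessment for it begins only once a catheter is out. Nor should the 8.0 points be read as the false difference: it is the gap between two codings under assumed prevalences.

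**Conclusion.** The point holds as a flaw in the outcome definition that should be corrected. As written, a non-leaking catheter user is scored continent, neither the imputation rule nor the separate analysis reliably prevents it, and the inclusion and analysis sections are not reconciled.

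Its size and direction cannot be derived from the documents. The 4.8 points under the current rule, and the 3.2 points the other way under the alternative coding, rest on assumed prevalences of 10% and 2%, 40% continence among the uncatheterised in both arms, and every catheter user answering *never*. With equal prevalence the between-arm difference does not depend on the coding, and what remains is an incontinence rate understated by up to the catheter prevalence. The documents do not show that the trial's result would be biased, only that the rule permits it.

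**What to change.** - Record whether a urinary catheter is in use (yes/no) at each assessment in all three arms, if this is not already collected.
- Amend *Ascertainment of outcomes* so that absence of incontinence requires *never* on Question 3 and no catheter in use at that assessment.
- Report catheter use by arm at each time point.
- Add two sensitivity analyses: one excluding catheter users, and one using the answer to Question 3 alone.
- Reconcile *Inclusion criteria for patients* with *Data analysis, Outcomes*: state which analysis set governs the primary analysis, and define the catheter group by criteria that apply equally in every arm and not by programme participation.

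The cost is at most one questionnaire item and a few lines of text. The downside is that the primary result will then partly reflect catheter use; reporting by arm and the sensitivity analyses make that visible.
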